### Study outcomes and measures

The primary outcomes are the incidence and prevalence of pressure ulcers. The secondary outcomes are the care staff’s knowledge and skills on preventing pressure ulcers. These outcomes will pertain to the cluster and individual participant levels.

PU incidence and prevalence: The incidence of PUs will be assessed using the validated PU incidence form [6]. The form will record the numbers, locations, and stages of the PUs that are detected. The common PU sites are numbered from 1 to 36 on a body map. The identification of stages will be adopted from the guidelines of the European Pressure Ulcer Advisory Panel and the National Pressure Ulcer Advisory Panel [7]. The prevalence of PUs will be evaluated using the validated prevalence form [6].

PU prevention knowledge: In this study, the knowledge test, which demonstrated good internal consistency and content validity, [8] will be adopted to assess the care staff’s knowledge of PU. The test has 30 true-false items, with each correct answer allocated a score of one. The range of scores is from 0 to 30, and the total score is 30. A higher score indicates a higher level of knowledge of PU.

PU prevention skill level: The skill checklist, which has good content validity and internal consistency, [8] will be used to assess the care staff’s skills on turning, positioning, transferring, lifting, and use of materials/devices for preventing pressure ulcers. The checklist lists the steps required to demonstrate the five different skills and the rating for the performance of the skill in each step using a 4-point scale: unsatisfactory (1), barely satisfactory (2), satisfactory (3), and very satisfactory (4). A higher total score indicates better skill at preventing PUs.

### Study procedures

The four trained RAs, who are registered nurses and will be blind to the group allocation, will collect the data. Each RA will be responsible for collecting the data for two nursing homes. The following data will be collected from both the experimental and control groups (Table 1). Immediately before (T0) the lecture, at the 8^th^ week (T1), and at the end of the implementation (T2) of the protocol (at the 16^th^ week of the implementation of the protocol), the staff participants will be assessed on their knowledge on preventing pressure ulcers in the presence of the RAs. Before the commencement of the skill training (T0), at the 8^th^ week (T1), and at the end (T2) of the implementation of the protocol (T3), the RAs will conduct an individual assessment of the staff participants’ skills on turning, positioning, transferring, lifting, and the use of preventive materials, while they are performing daily care for residents.

**Table 1 Tab1:** Data collection

Study outcomes	Before the lecture	Before the skill training	Immediately before commencement of protocol implementation	8^th^ week after the protocol	At the end of the protocol
Knowledge	✓			✓	✓
Skills		✓		✓	✓
Prevalence	✓		✓	✓	✓
Incidence “-------------------------------the whole period					

In assessing the incidence of PUs, the RAs will inspect the skin of each resident two times a week to detect the first PUs (on residents without PUs) and new PUs (on residents already suffering from PUs), starting from before the intensive training course to the end of the implementation of the protocol. The size, location, and stage of PUs will be assessed when they are detected. The prevalence of PUs will be evaluated by the RAs before the commencement of the intensive training course (T0), immediately before the commencement of the implementation of the protocol (T1), at the 8^th^ week (T2), and at the end (T3) of the implementation of the protocol. An inter-rater agreement of at least 90 % among four RAs will be obtained for the skill checklists and PU assessment (size, location, and stage) before the skill-training sessions.

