The two-hour lecture will be directed towards HWs and PCWs and cover such topics as PU etiology and assessment, risk factors for the development of PU, PU risk assessments, skin assessments, evidence-based preventive interventions, and the association between daily personal care and PU prevention. The two skill-training sessions will consist of one three-hour training session for HWs and PCWs, and one two-hour training session for HWs only. The contents of the two skill-training sessions have been tailor-made for each type of care staff based on their different duties as noted in the protocol. In the three-hour session, HWs and PCWs will be trained in such skills as turning, positioning, lifting, transferring, the use of pressure-relieving devices, and skin assessments, while the two-hour session for the HW group will cover PU risk assessments using the PU risk form and PU assessments. A return demonstration of the skills will be carried out by the participants to ensure that they are able to perform the skills accurately. As the intensive training course (the lecture and two skill-training sessions) is considered to be in-service training that will enrich their knowledge and skills to improve the quality of care in preventing pressure ulcers, all HWs and PCWs in the experimental group will be required to attend the course. However, their participation in this study will be voluntary. Acting as supervisors of HWs and PCWs, nurses, if available in the experimental group, will required to attend the course so that they will know what HWs and PCWs are learning. Nurses will not be participants in this study. This intensive training course for the four nursing homes in the experimental group will be conducted by the PI and another researcher involved in this study.

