### Randomization

Randomization will be carried out after the written informed consent of all individual residents to participate this study has been obtained and the recruitment of residents from the eight nursing homes has been completed. The PI will assign each nursing home that has agreed to join the study a number of from one to eight. A trained RA using the random number generator will randomly assign four numbers to the experimental group and the remaining four numbers to the control group. In accordance with the randomized numbers, the PI will assign the eight nursing homes to the experimental or control groups.

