### Blinding

Only the four trained RAs who will be responsible for data collection will be blind to the group allocation. The PI and the care staff in the eight nursing homes will not be blind to the group allocation.

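### The assessors are said to be blind, but their baseline visits are timed by training events that only experimental homes have, which is likely to reveal the arm before most ulcers are counted

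*Protocol article*

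**What the plan says.** All references are to the protocol article.

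- **Blinding is claimed twice.** Study procedures: "The four trained RAs, who are registered nurses and will be blind to the group allocation, will collect the data". Blinding: "Only the four trained RAs who will be responsible for data collection will be blind to the group allocation". The next sentence there adds: "The PI and the care staff in the eight nursing homes will not be blind to the group allocation".
- **Baseline is tied to training events.** Under Study procedures the T0 knowledge test is set "Immediately before (T0) the lecture", and at that point "the staff participants will be assessed on their knowledge on preventing pressure ulcers in the presence of the RAs". The T0 skill rating comes before the skill training. Prevalence is surveyed before the course and again immediately before protocol implementation begins. Table 1 uses the same events as its column labels for both groups.
- **The events exist in one arm.** Interventions: "This intensive training course for the four nursing homes in the experimental group will be conducted by the PI and another researcher". Control homes give usual care, and no lecture, skill session or protocol start is described for them.
- **The same RAs count the primary outcome.** "Each RA will be responsible for collecting the data for two nursing homes". They inspect every resident's skin twice a week from before the course to the end of the protocol.
- **Order of the draw.** Randomization: "Randomization will be carried out after the written informed consent of all individual residents to participate this study has been obtained". No section places T0 before or after the draw.

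**The concern.** Only the data collectors are meant to be blind in this trial. Detecting and staging an ulcer, and rating each step of a skill on a 4-point scale, are judgements. If an RA knows which homes were trained, part of a difference in ulcers or skills could come from the assessor and not from the programme.

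An RA asked to run a test just before a lecture can infer that the home is experimental. An RA whose other home has no such event can infer the opposite. The schedule therefore works against the blinding that the same article claims.

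The second consequence concerns the baseline. Which homes get a lecture is known only after the draw. A test just before the lecture would therefore normally be taken after allocation, on staff who know their arm, and would not be a true pre-randomisation measurement.

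**Working it through.** The plan gives no figure on this point, so there is nothing to reproduce. The check is a comparison of sections, followed by an illustration of scale.

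**1. Does each early time point exist in both arms?**

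| RA assessment | Anchor in Study procedures / Table 1 | Experimental home | Control home |
|---|---|---|---|
| Knowledge, T0 | immediately before the lecture | defined | not defined |
| Skills, T0 | before the skill training | defined | not defined |
| Prevalence, first survey | before the course | defined | not defined |
| Prevalence, second survey | immediately before protocol start | defined | not defined |

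Data are to be collected in both groups at these points, so control homes need an equivalent date. None is given, and no safeguard such as matched dates is described.

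**2. When would the arm become apparent, relative to the counting?** Skin inspections and the first prevalence survey begin before the course, so some counting precedes any disclosure. What follows is the 16-week protocol at two inspections a week, 16 × 2 = 32 inspections per resident, and the comparison at the end of implementation named in Hypotheses. The length of the lead-in before the course is not stated. That most of the counting comes afterwards assumes that this lead-in is shorter than the period that follows.

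**3. Where does T0 fall relative to the draw?** Recruitment of residents and staff is completed, then homes are drawn, then the experimental homes are trained. A test immediately before the lecture therefore normally follows the draw. This is an inference from the order of events; the article does not state it.

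**4. Scale, on assumed under-calling rates.** Inputs from Sample size: incidence 9.5 % and 6 % (a planned difference of 3.5 points) and 392 residents per group. Assume no true effect, with 9.5 % in both arms, and that RAs miss a fraction f of ulcers in experimental homes. The fraction and its direction are assumptions with no source in the document.

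- Observed experimental incidence: p₂ = 9.5 % × (1 − f); spurious difference d = 9.5 % − p₂.
- Rejection rate of a two-sided 0.05 test: Φ((d − 1.96·SE₀)/SE₁) + Φ((−d − 1.96·SE₀)/SE₁), where SE₀ uses the pooled proportion and SE₁ the two separate ones, n = 392 per group, clustering ignored.
- f = 0.10: p₂ = 8.55 %, d = 0.95 points, 0.95/3.5 = 27 % of the planned effect. SE₀ = 0.02047, SE₁ = 0.02046; Φ(−1.50) + Φ(−2.42) = 7.5 %.
- f = 0.20: p₂ = 7.6 %, d = 1.9 points, 1.9/3.5 = 54 %. SE₀ = 0.01997, SE₁ = 0.01996; Φ(−1.01) + Φ(−2.91) = 15.8 %.
- To mimic the whole planned effect: f = 1 − 6/9.5 = 37 %, that is about 14 of the 37 ulcer cases expected in 392 residents (392 × 0.095 = 37.2; 392 × 0.06 = 23.5).

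**The case against.** The strongest reply is that disclosure is inferred. Both groups are assessed at the same nominal points. Nothing says that RAs attend the lecture or are told of it, and the course is given by the principal investigator and another researcher. Visits on matched dates would fit the text and keep the arm hidden. The word 'immediately' applies to the knowledge test and the second prevalence survey, not to the skill rating or the first survey. Visit logistics are often left to a full protocol, which is not shown here.

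All of this stands as a limit on how firmly the point can be put. It does not remove it, because the article does fix its visit times, fixes them by events in one arm, and leaves control homes without an anchor.

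Other safeguards also count. The incidence and prevalence forms are validated, ulcer sites are numbered on a body map, staging follows a guideline, inter-rater agreement of at least 90 % is required, and the knowledge test is true-false. These narrow the room for judgement but do not replace blinding.

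A further reply is that RAs may learn the arm anyway, since they are in the homes twice a week and watch unblinded staff give care. That is correct, and re-timing baseline does not close that route.

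A reader might also infer that RAs know the arm before any ulcer is counted, or that T0 is stated to be post-allocation. The article supports neither: inspections start before the course, and T0 is nowhere placed relative to the draw.

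**Conclusion.** The point holds as a conflict between the claimed assessor blinding and the stated visit schedule. Baseline knowledge, baseline skills and the two early prevalence surveys are anchored to events that only experimental homes have and that are undefined for control homes. Followed as written, the schedule is likely to reveal the arm to RAs before most of the incidence counting and before the end-of-protocol comparison, and it normally places T0 after allocation on staff who are not blind.

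This rests on two inferences: that RAs can tell from the timing whether a lecture or training follows, and that training dates in practice follow the draw. It does not show that bias will occur or how large it would be. The differences of 0.95 and 1.9 points, and the rejection rates of 7.5 % and 15.8 %, describe only what assumed under-calling of 1 in 10 and 1 in 5 would do. The matter should be settled before data collection, because a baseline taken after allocation cannot be retaken.

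**What to change.** In Study procedures and Table 1:

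1. Take T0 knowledge, skills and prevalence in all eight homes in one common calendar window, after recruitment of residents and staff has closed and before the draw described under Randomization. Complete the inter-rater agreement check, now due before the skill-training sessions, before this window.
2. Define the later assessments (pre-protocol prevalence, week 8 and week 16) by calendar weeks common to all homes.
3. Give RAs visit dates only, without training dates.

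In Blinding, and in the matching sentence of Study procedures, state only that RAs are not told the allocation. The steps above remove the disclosure built into the schedule, but twice-weekly inspections alongside unblinded staff mean that blinding cannot be guaranteed.

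A rule keeping RAs away from homes around training days is not proposed. With 1088 residents and four RAs, each covers 1088/4 = 272 residents, or 272 × 2 = 544 inspections a week, which leaves little room for it.

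Cost: the draw and the first training day move back by the length of the T0 window. No extra residents, staff or visits are needed. The gain is a true pre-randomisation baseline with the same meaning in both arms.

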**Methods/design:**

This is a two-arm cluster randomized controlled trial with an estimated sample size of 1088 residents and 74 care staff from eight for-profit private nursing homes. Eligible nursing homes will be those classified as category A2 homes in the Enhanced Bought Place Scheme (EBPS), having a capacity of around 130–150 beds, and no structured PU prevention protocol and/or programmes in place. Care staff will be health workers, personal care workers, and nurses who are front-line staff providing direct care to residents. Eight nursing homes will be randomly assigned to either an experimental or control group. The experimental group will be provided with an intensive training programme and will be involved in the implementation of a 16-week pressure ulcer prevention protocol, while the control group will deliver the usual pressure ulcer prevention care. The study outcomes are the pressure ulcer prevention knowledge and skills of the care staff and the prevalence and incidence of pressure ulcers. Data on the knowledge and skills of care staff, and prevalence of pressure ulcer will be collected at the base line, and then at the 8^th^ week and at completion of the implementation of the protocol. The assessment of the incidence of pressures will start from before the commencement of the intensive training course to the end of the implementation of the protocol.

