### Hypotheses

The experimental group will have a lower incidence and prevalence of PUs than the control group at the end of the implementation of the protocol.The care staff in the experimental group will have more PU knowledge than the care staff in the control group at the 8^th^ week, and at the end of the implementation of the protocol.The care staff in the experimental group will have higher-level PU prevention skills than the care staff in the control group at the 8^th^ week, and at the end of the implementation of the protocol.

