### Interventions

The interventions for both the experimental and control groups pertain to the cluster level and the individual participant level.

In the control group, the care staff will provide residents with the usual PU prevention care, which is a series of personal care activities that include perineal care, the repositioning of residents, skin moisturization, and the sitting out of residents.

The experimental group will be involved in the implementation of the comprehensive PU prevention programme, the aim of which is to equip care staff with PU prevention knowledge and skills, and to guide care staff including HWs and PCWs, in PU prevention. This programme is the same as the previous programme that was pilot tested [8, 9]. It consists of two major components: an intensive training course (a two-hour lecture and two skill-training sessions) and a PU prevention protocol.

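### Skills T0 appears to follow the experimental arm's lecture, so any lecture effect on the rated skills would bias the GEE group-by-time contrast towards no effect (minor)

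*Protocol article*

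**What the plan says.** **Timing of the baselines.** Study procedures sets three T0 points:
- Knowledge: "Immediately before (T0) the lecture".
- Prevalence: "before the commencement of the intensive training course (T0", which Table 1 places in its pre-lecture column.
- Skills: "Before the commencement of the skill training (T0". Table 1 ticks skills only in the next column, the one for the time before skill training.

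The abstract treats all three as one time point: "Data on the knowledge and skills of care staff, and prevalence of pressure ulcer will be collected at the base line".

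**The lecture.** Interventions defines the programme as "an intensive training course (a two-hour lecture and two skill-training sessions) and a PU prevention protocol", delivered to the experimental homes. Lecture topics include "evidence-based preventive interventions, and the association between daily personal care and PU prevention". The three-hour session that follows is where staff are "trained in such skills as turning, positioning, lifting, transferring, the use of pressure-relieving devices, and skin assessments".

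**Hypothesis and analysis.** The third hypothesis is that experimental staff will have "higher-level PU prevention skills than the care staff in the control group at the 8^th^ week, and at the end of the implementation". Statistical analysis plans an independent t-test between groups for knowledge and skills. It also plans a GEE over time with a group-by-time interaction, adjusted for clustering and possible confounders. Below, T1 and T2 mean week 8 and the end of implementation, as in the knowledge schedule.

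**The concern.** A baseline should precede every part of the intervention under test. As scheduled, knowledge and prevalence meet that standard and skills appears not to. At skills T0 the experimental staff would already have attended a lecture on preventive interventions and daily care. The skills are then scored during daily care. Control staff would have received nothing.

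If the lecture improves the rated skills at all, T0 rises in one arm only. A group-by-time contrast measured from T0 then subtracts that gain from the programme's estimated effect. Adjusting for T0 skills would remove part of it too. This matters because the GEE is the only planned analysis of skills that allows for clustering. A pre-lecture score that was never measured cannot be recovered in the analysis.

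The skills T0 is also tied to a training date that control homes do not have, so its timing there is undefined.

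**Working it through.** **Step 1: order of events.** Prevalence T0 falls before the intensive course in the text and before the lecture in Table 1, so the lecture opens the course. Table 1 then has a separate column for the time before skill training, placed between the pre-lecture column and the one immediately before protocol implementation. Skills is ticked there and not in the pre-lecture column. Two columns are needed only if the two times differ, so the natural reading is that skills T0 follows the lecture. No sentence says so, and the interval is not given.

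**Step 2: the plan's own staff numbers.** Inputs from Sample size: d = 0.95 (knowledge) and 1.13 (skills), 80 % power, alpha 0.05 (two-sided taken), 30 % drop-out, 70 % recruitment. The normal formula is n per group = 2(1.96 + 0.84)² / d².
- Knowledge: 15.70 / 0.9025 = 17.4, rounded up to 18. This matches the plan.
- Skills: 15.70 / 1.277 = 12.3, rounded up to 13. Knowledge therefore drives the number.
- Inflation: 18 / (0.7 × 0.7) = 36.7, rounded up to 37 per group, 74 in all. This matches the plan.

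The timing of skills T0 does not affect these figures.

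**Step 3: comparison at follow-up.** A between-group comparison at T1 or T2 does not use T0. The expected d stays 1.13, and t-test power at 18 per group is 91 %, whatever the lecture does.

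**Step 4: change from T0.** Let f be the share of the skills effect already present at T0 in the experimental arm, and r the correlation between T0 and follow-up. The documents give neither, so both are assumed. In units of the cross-sectional SD:
- Expected difference in change = 1.13 × (1 − f): 1.13 at f = 0, 1.02 at f = 0.10, 0.85 at f = 0.25.
- SD of change = √(2(1 − r)): 1.18 at r = 0.3, 1.00 at r = 0.5, 0.77 at r = 0.7.

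Two-sample t-test power at 18 per group, clustering ignored:

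| r | f = 0 | f = 0.10 | f = 0.25 |
|---|---|---|---|
| 0.3 | 80 % | 71 % | 55 % |
| 0.5 | 91 % | 84 % | 70 % |
| 0.7 | 99 % | 97 % | 89 % |

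**Step 5: adjustment for T0 skills, if done.** The expected adjusted difference is 1.13 × (1 − r × f). At r = 0.5 this gives 1.13 × 0.95 = 1.07 for f = 0.10 and 1.13 × 0.875 = 0.99 for f = 0.25. The bias has the same direction as in Step 4 but is smaller.

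**The case against.** **The skills hypothesis does not depend on T0.** A reader might infer that it is tested against a contaminated baseline. It is worded as a between-group difference at week 8 and at the end, and the planned t-test at those times does not use T0. This objection stands in full: only the GEE group-by-time contrast, or an adjustment for T0 skills, is exposed. Its limit is that the t-test ignores clustering, so the exposed analysis is also the planned cluster-adjusted one.

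**The lecture may not move the score.** A reader might also infer that part of the effect is in fact absorbed at T0. The checklist rates turning, positioning, transferring, lifting and use of materials or devices. These are taught in the three-hour session with return demonstration, not in the lecture. The absorbed share may be near zero. This stands too: the documents support a possible bias, not a demonstrated one.

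**The order is inferred, and adjustment for T0 is not announced.** An assessment made before the lecture would also be before the skill training. The plan names possible confounders without saying that T0 skills is one. Both points are fair. Table 1 still points one way on the order, and the text does not correct it.

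**Knowledge T0 also falls after randomization, with staff unblinded.** As scheduled, that is so. Awareness of allocation therefore does not set skills apart, and moving skills T0 ahead of the lecture would not by itself remove it.

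**Conclusion.** The point holds in a limited form. As Table 1 reads, the skills T0 is not a pre-programme measurement in the experimental arm, unlike the T0 for knowledge and prevalence. If the lecture improves the rated skills, the group-by-time contrast understates the programme's effect by the share already gained. The follow-up comparison that the hypothesis describes is untouched.

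The size cannot be derived from the documents. The fall from 91 % to 84 % or 70 % power is an illustration for assumed shares of 10 % and 25 %, an assumed correlation of 0.5 and no clustering. With the correlation between 0.3 and 0.7, power at a 10 % share runs from 71 % to 97 %. These figures do not show that the trial is underpowered for skills.

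Severity is minor. Skills is a secondary outcome, and a positive lecture effect at T0 makes the change contrast conservative, so it would not favour the programme.

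**What to change.** In Study procedures and Table 1, move the skills T0 assessment to before the lecture, alongside the knowledge T0 test. Take it at a matched calendar time in control homes. If feasible, complete it in all eight homes after consent and before the randomization draw, which would also remove awareness of allocation at T0. Bring forward the 90 % inter-rater agreement, now due before the skill-training sessions, so that it is in place before this assessment.

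While editing that sentence, reconcile the time labels: it marks the end of implementation as both T2 and T3.

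The cost is scheduling. No assessment is added, but skills are observed individually during daily care, so these observations and the rater training must be organised earlier than now planned. If the move is impossible, the protocol should say that skills T0 is post-lecture in the experimental homes and rest the skills hypothesis on the between-group contrasts at week 8 and at the end, with allowance for clustering.

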### Participants

The clusters are nursing homes. There will be eight private for-profit NHs in Hong Kong. They will be those that have been classified as category A2 homes in the Enhanced Bought Place Scheme (EBPS) and eager to improve the pressure ulcer prevention care that they currently offer, have a capacity of around 130–140 beds, and have no PU prevention protocol in place. We believe that EBPS-A2 homes will represent the target population of for-profit private NHs in Hong Kong because they hire few or no professional nurses but are considered more motivated to improve the quality of the care that they provide than non-EBPS homes, and would perhaps therefore be more likely than the latter to comply with the protocol. The study sample will be the residents and care staff from the eight private for-profit NHs in Hong Kong. The residents will be those aged 60 or above and the care staff will include personal care workers (PCWs) and health workers (HWs) who provide direct care to residents.

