### Statistical analysis

IBM SPSS Statistics 22 will be used to analyse the data. An intention-to-treat analysis will be adopted. Descriptive statistics such as mean or percentage will be used to summarize PU prevention knowledge and skills, and the prevalence and incidence of PUs. A chi-square test will be performed to compare the PU prevalence and PU incidence of residents between the two groups. An independent t-test will be adopted to compare the knowledge and skills of care staff between the two groups. Generalized estimating equation (GEE) will be used to compare the two groups in terms of their performance in the knowledge and skills tests, as well as in PU status over time, and to examine the groups by the time interaction effect, adjusting for the cluster effect and possible confounders. Significance will be set at a P value of < =0.05.

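### The primary incidence comparison mixes residents with and without an ulcer at entry, and its chi-square test ignores the baseline ulcer status that the trial collects

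*Protocol article*

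**What the plan says.** Study outcomes and measures makes incidence a primary outcome: "The primary outcomes are the incidence and prevalence of pressure ulcers". For incidence, the same section says of the form: "The form will record the numbers, locations, and stages of the PUs that are detected".

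The only working description of incidence is in Study procedures. Assessors make twice-weekly skin inspections with two targets: "to detect the first PUs (on residents without PUs) and new PUs (on residents already suffering from PUs"). The counting window is described separately as "starting from before the intensive training course to the end of the implementation of the protocol". That section also plans a survey of existing ulcers at the start of this window: "The prevalence of PUs will be evaluated by the RAs before the commencement of the intensive training course (T0").

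Participants sets one resident criterion, "The residents will be those aged 60 or above", and states no exclusion for an existing ulcer.

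Statistical analysis gives the between-arm test: "A chi-square test will be performed to compare the PU prevalence and PU incidence of residents between the two groups". It adds a GEE for staff test performance and ulcer status over time, "adjusting for the cluster effect and possible confounders". The confounders are not named. Randomization draws four of the eight homes for the programme, with no stratification or matching stated.

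**The concern.** A resident who already has an ulcer can be expected to have a higher risk of another than a resident with intact skin. The article places both in one incidence assessment, and the named test compares the arms without distinguishing them. The result then depends partly on how many residents in each arm had an ulcer at the start.

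Randomisation balances this only on average, and eight homes allow a noticeable chance difference. Such a difference could look like part of a programme effect or hide part of one. The information needed to correct it is collected at T0, before any part of the programme begins, but the stated incidence test does not use it.

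**Working it through.** **The plan's own effect.** Sample size takes incidence falling from 9.5 % to 6 %, a difference of 3.5 points. The odds ratio is (0.06/0.94)/(0.095/0.905) = 0.608; the protocol gives 0.60. This is the yardstick below.

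**Inputs that the documents do not give.** They state neither an expected baseline prevalence nor the risk of a further ulcer in a resident who already has one. The following are assumptions:
- prevalence π at T0 centred on 10 %;
- risk of at least one new ulcer during follow-up, r₁ in residents with an ulcer and r₀ in those without: (20 %, 8 %), (25 %, 7 %) or (35 %, 6 %).

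At π = 10 % these give overall incidence of 9.2 %, 8.8 % and 8.9 %, close to the protocol's 9.5 %.

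**Share of cases from residents ulcerated at entry.** The share is πr₁ / [πr₁ + (1−π)r₀]. At π = 10 %:
- 0.020/0.092 = 22 %
- 0.025/0.088 = 28 %
- 0.035/0.089 = 39 %

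**Apparent effect when the programme does nothing.** Overall incidence in an arm is πr₁ + (1−π)r₀. With π = 8 % in the experimental arm and 12 % in the control arm:

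| r₁, r₀ | Experimental | Control | Odds ratio |
|---|---|---|---|
| 20 %, 8 % | 8.96 % | 9.44 % | 0.944 |
| 25 %, 7 % | 8.44 % | 9.16 % | 0.914 |
| 35 %, 6 % | 8.32 % | 9.48 % | 0.867 |

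On the log scale this is ln 0.944 / ln 0.60 = 11 % to ln 0.867 / ln 0.60 = 28 % of the planned effect.

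**How likely is a 4-point gap?** The protocol's 392 residents per group over four homes is 98 per home. The standard deviation of the arm difference in prevalence is √[2 × 0.1 × 0.9/392 × (1 + 97 × ICC)].
- At the protocol's ICC of 0.001 it is 0.0224, so a gap above 4 points in either direction has probability of about 7.5 %.
- At an ICC of 0.01 the probability is about 18 %.
- At an ICC of 0.03 it is about 35 %.

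The two larger ICCs are assumptions.

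**A larger gap.** Prevalence of 6 % against 14 % would give odds ratios of 0.75 to 0.89. A gap above 8 points has probability of about 0.04 %, 0.8 % and 6 % at the same three ICCs, so it is not the realistic case.

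**A second set of assumptions.** Fix control incidence at 9.5 %, let control prevalence run from 5 % to 20 %, and let the relative risk in ulcerated residents run from 2 to 5. A prevalence 5 points lower in the experimental arm then gives incidence of about 7.9 % to 9.1 % there. That is an odds ratio of 0.82 to 0.95, or 11 % to 45 % of the 3.5-point design difference. The top of this range needs 5 % prevalence in one arm and none in the other.

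**The case against.** Several stronger readings are tempting, and the text does not support them.

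- **That the plan states it will sum the two event types into one figure.** It does not. The sentence describes what assessors look for, and the form would allow separation. A single figure is the natural reading, because nothing narrows it, but it is a reading.
- **That ulcers are counted, so one resident contributes several events and the chi-square independence assumption fails within residents.** The analysis sentence refers to incidence of residents, and the sample size uses percentages of residents. The resident is the likely unit, so this failure is hypothetical.
- **That baseline burden biases the result.** Ulcer burden at entry is not caused by allocation, so a difference is chance, not systematic. The part due to individual residents is already within the sampling error of an unadjusted test. The part due to variation between homes is not, because the chi-square ignores clustering.
- **That the plan has no adjusted analysis.** It has a GEE with cluster and confounder adjustment, and the chi-square is not labelled the primary analysis.
- **That residents with an ulcer at entry should leave the denominator.** The programme covers all residents of a home, and preventing further ulcers is a legitimate aim. Removing them would change the target population.

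These objections limit the point but do not remove it. The GEE is described for ulcer status over time, and neither incidence nor baseline ulcer status is named in it. The only test stated for incidence is the unadjusted chi-square.

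**Conclusion.** The point holds in a limited form. The primary incidence takes in residents with and without an ulcer at entry, and the test stated for it ignores a prognostic factor that the trial measures. With four homes per arm, a chance imbalance can pass into the comparison in either direction.

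The realistic size is modest: a spurious odds ratio of about 0.87 to 0.94 for a 4-point prevalence gap, against a planned 0.60. Such a gap has probability of about 7.5 % at the protocol's own ICC, and more if homes differ more than that ICC allows. All these sizes rest on assumed prevalence and risks. This is a worthwhile improvement to the primary comparison, and it does not show that the planned result would be invalid.

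**What to change.** 1. In Study outcomes and measures, define incidence per resident: at least one new ulcer during follow-up, each resident counted at most once.
2. In Statistical analysis, make the main incidence comparison a cluster-adjusted model, with the home as cluster and ulcer status at T0 as covariate, in place of the unadjusted chi-square. The planned GEE can serve if incidence and this covariate are named in it. With only eight homes, its standard errors need a small-sample correction.
3. Report incidence separately for residents with and without an ulcer at T0.
4. In Sample size, confirm that the 9.5 % and 6 % from the earlier study use the same definition, and say so.

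The cost is a few sentences. The T0 survey and the incidence form already supply the data, and no resident leaves the analysis.
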